### Inclusion and exclusion criteria

Children from 6 to 13 years old with mild to moderate intellectual disability in line with DSM-V criteria and behavioral problems are eligible for this study. Detailed inclusion and exclusion criteria are summarized in Table 1. Pychotropic medications and occupational, speech, orthoptic and/or psychomotor therapies should remain unchanged thorough the protocol. The intervention will be discontinued in case of clinical aggravation, patient’s refusal to continue or after more than two unjustified absence rated by therapist.

**Table 1 Tab1:** Inclusion and exclusion criteria

Inclusion criteria	Exclusion criteria
• age between 6 years 0 month and 13 years 11 months • ABC scale total score equal or higher than 15 • total IQ score between 45 and 70 (WPPSI-III, WPPSI-IV, WISC-IV or WISC-V scale) AND standard score of at least one domain of the VABS-II between 40 and 70 AND measurements carried out for less than 18 months • French speaker • Psychotropic medication remained unchanged for 1 month • Occupational, speech, orthoptic and/or psychomotor therapies remained unchanged for 1 month	• DSM-5 criteria for autism spectrum disorder • vascular, infectious or degenerative neurological condition • medication for somatic problem that might interfere with brain functioning

*WPPSI* Wechsler Preschool and Primary Scale of Intelligence (Wechsler, 2004; 2014), *WISC* Wechsler Intelligence Scale for Children (Wechsler, 2005; 2016), *ABC* Aberrant Behavior Checklist (Aman & Singh, 1986), *VABS-II* Vineland Adaptive Behavior Scales – Second Edition (Sparrow, Cicchetti, & Balla, 2015)

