### Assessments and outcomes

Assessments will include behavioral problems, neurocognitive abilities (language, memory, praxis and visuospatial abilities and attentional and executive functions), social cognitive processes (emotion recognition and theory of mind abilities) and functional outcome (quality of life, self-esteem and adaptive and daily living skills) measures. Assessments will involve the child, their parents and an experienced psychologist.

The primary outcome is the change from the baseline of the score on the “hyperactivity – noncompliance” subscale of the Aberrant Behavior Checklist [26].

Secondary outcomes are as follows:the change from the baseline of the scores for a semi-structured interview investigating adaptive behaviors and daily living skills,the change from the baseline of the scores of two questionnaires investigating quality of life and self-esteem,the change from the baseline of scores of paper-and-pencil subtests, computerized subtests and questionnaires investigating praxis and visuospatial functions, memory, language, attentional and executive functions, and social cognition, andthe change of all scores from post-treatment to the 6-month follow up.

See Table 2 for a detailed overview of the assessments and outcome measures.

**Table 2 Tab2:** Measurements

	Kind of measure	Name	type	informant	recruitment	baseline assessment	post-treatment assessment	6-months follow up assessment
	IQ estimation	WPPSI-III, WPPSI-IV, WISC-IV or WISC-V	P&P	C	*			
*primary outcome*	behavioural problems	ABC	Q	P	*	*	*	*
*secondary outcome*	adaptive and daily living skills	VABS-II	S Int.	P	*	*	*	*
	quality of life	KIDSCREEN-27	Q	P		*	*	*
	self esteem	self-esteem subscale MDI-C	Q	C		*	*	*
	lexical knowledge	PPVT	P&P	C		*	*	*
	learning and long term memory	word list CMS	P&P	C		*	*	*
		dot locations CMS	P&P	C		*	*	*
	praxis and visuospatial functions	visuomotor precision NEPSY-II	P&P	C		*	*	*
		imitating hand positions NEPSY-II	P&P	C		*	*	*
		arrows NEPSY-II	P&P	C		*	*	*
		block construction NEPSY-II	P&P	C		*	*	*
		route finding NEPSY-II	P&P	C		*	*	*
	attentional functions	sky search TEA-Ch	P&P	C		*	*	*
		alertness TAP 2.3	CT	C		*	*	*
		auditory attention NEPSY-II	P&P	C		*	*	*
		divided attention TAP 2.3	CT	C		*	*	*
	executive functions	Go/NoGo TAP 2.3	CT	C		*	*	*
		response set NEPSY-II	P&P	C		*	*	*
		inhibition NEPSY-II	P&P	C		*	*	*
		mazes WISC-III	P&P	C		*	*	*
	social cognition	affect recognition NEPSY-II	P&P	C		*	*	*

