### Sample size

To our knowledge, only one previous study has evaluated the effectiveness of a non-drug treatment using the “hyperactivity – noncompliance” score of the ABC as the primary outcome measurement [27]. A decrease of 3 points after treatment was found to be significant (M = 12.1; SD = 8.9 versus M = 9; SD = 7.4). Therefore, we hypothesize that following the motor skills and video viewing intervention, we will observe a 3 point decrease of the “hyperactivity – noncompliance” score. We expect that the decrease will be double for the «COGNITUS & MOI» program: the difference between the two treatments would be at least 3 points. With an expected SD of 5, a power of 90%, 1:1 allocation into the two groups, two-sided testing and a significance level of 5%, a total sample of 126 participants is required. Given the insufficient information from the literature and the risk of dropout, 200 participants will be enrolled in the present study.

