### Statistical analysis

Descriptive statistics will be reported for each variable of interest for the two groups.

First, independent-sample t-tests or non-parametric Mann-Whitney tests will be run to assess the lack of differences between groups in age, IQ or severity of ABC scores at baseline (*p* < 0.05, two-sided).

Second, independent-sample t-tests or non-parametric Mann-Whitney tests will be run to compare the “hyperactivity – noncompliance” score change from the baseline to post-treatment assessment in the two groups (*p* < 0.05, two-sided).

Third, similar tests will be run for each secondary outcome measure. The score changes will be separately considered from the baseline to post-treatment assessment and from the post-treatment to 6-month follow-up assessment (*p* < 0.05, two-sided).

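### The ABC is scheduled twice before treatment, but the recruitment score has no stated role in the primary analysis, so some avoidable rating error may remain (lost precision, not bias)

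*Protocol article*

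**What the plan says.** In the Protocol article, the Table 2 row "behavioural problems ABC Q P" is marked in all four timing columns: recruitment, baseline, post-treatment and 6-month follow-up. The informant is the parent. Table 1 explains the recruitment rating: entry requires "ABC scale total score equal or higher than 15".

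The section Assessments and outcomes begins its definition with "The primary outcome is the change from the baseline of the score on the" and names the hyperactivity-noncompliance subscale. The section Statistical analysis then compares the "score change from the baseline to post-treatment assessment in the two groups" by independent-sample t-test or Mann-Whitney test. It names no covariate, and the recruitment rating is not mentioned.

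The section Sample size assumes that "the difference between the two treatments would be at least 3 points". "With an expected SD of 5", 90% power and a two-sided 5% level, it concludes that "a total sample of 126 participants is required". Enrolment is raised to 200 because the literature is thin and children may drop out.

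**The concern.** A raw change score carries the full error of whichever single pre-treatment rating is subtracted. Here the schedule provides a second pre-treatment rating on the same instrument from the same type of informant. If that rating holds information about the post-treatment score beyond what baseline holds, adjusting for it narrows the confidence interval for the primary difference without recruiting another child.

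What is at stake is precision only. Selection on the recruitment total comes before randomisation and acts alike in both arms, so any regression to the mean that it causes is equal in expectation between arms. Precision could still matter, because the plan itself names insufficient literature as a reason for enrolling more than the calculated number.

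**Working it through.** **1. The plan's own figure.** Inputs from Sample size: difference 3, SD 5 (read as the SD of change), power 90%, two-sided 5%, 1:1.
- Normal formula: 2 × (1.960 + 1.282)² × 25/9 = 58.4, so 59 per arm, 118 in total.
- Exact t-test: 59.35, so 60 per arm, 120 in total.
- t-test figure divided by the Mann-Whitney efficiency 3/π: 59.35 × π/3 = 62.15, so 63 per arm, 126 in total.

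The stated 126 is therefore reproduced as a t-test size inflated for the Mann-Whitney option.

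**2. Power at the enrolled size.** With 100 per arm, 3 / (5 × √(2/100)) = 4.243, and Φ(4.243 − 1.960) = 0.989.

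**3. What the second rating adds.** The correlations are assumptions, since the documents give none. Take unit variances and let b be the baseline-post correlation, c recruitment-post and d recruitment-baseline.
- Raw change: 2(1 − b)
- Change from the mean of the two ratings: 1 + (1 + d)/2 − (b + c)
- ANCOVA on baseline: 1 − b²
- ANCOVA on both: 1 − (b² + c² − 2bcd)/(1 − d²)

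| b, d, c | Raw change | Change from mean of two | ANCOVA, baseline | ANCOVA, both | Cut from second covariate |
|---|---|---|---|---|---|
| 0.5, 0.5, 0.5 | 1.00 | 0.75 | 0.750 | 0.667 | 11% |
| 0.8, 0.8, 0.8 | 0.40 | 0.30 | 0.360 | 0.289 | 20% |
| 0.7, 0.7, 0.6 | 0.60 | 0.55 | 0.510 | 0.486 | 5% |
| 0.8, 0.8, 0.64 | 0.40 | 0.46 | 0.360 | 0.360 | nil |

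The last row is serial decay (c = b × d): recruitment relates to post-treatment only through baseline. The second covariate then adds nothing, and the mean-of-two change score is worse than the raw change, by 0.46/0.40 − 1 = 15%.

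**4. Translation to power at 100 per arm, difference 3.** The raw-change SD is scaled by the square root of the variance ratio from the table, using the normal approximation.

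| SD of change | b, d, c | Raw change | ANCOVA, baseline | ANCOVA, both |
|---|---|---|---|---|
| 5 | 0.8, 0.8, 0.8 | 98.9% | 99.4% | 99.9% |
| 8 | 0.5, 0.5, 0.5 | 75.5% | 86.5% | 90.1% |
| 8 | 0.8, 0.8, 0.8 | 75.5% | 79.8% | 87.7% |
| 8 | 0.7, 0.7, 0.6 | 75.5% | 82.0% | 83.8% |
| 8 | 0.8, 0.8, 0.64 | 75.5% | 79.8% | 79.8% |

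The move from raw change to ANCOVA on baseline is a separate gain. Only the last step belongs to the recruitment rating.

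**5. Could the SD of change exceed 5?** The SDs of 8.9 and 7.4 cited in Sample size give a change SD of 5 only if the pre-post correlation is (8.9² + 7.4² − 5²) / (2 × 8.9 × 7.4) = 108.97/131.72 = 0.83. At an assumed correlation of 0.6 the change SD would be √(133.97 − 0.6 × 131.72) = 7.4, and at 0.5 it would be 8.25. An SD of 8 in step 4 is thus an assumption, not a figure in the plan.

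**The case against.** The strongest reply is that nothing here is an error. The outcome is defined consistently as change from baseline, and it is conventional to keep a screening score for eligibility and analyse the rating labelled baseline. On the plan's inputs, power is already about 99%. The t-test and the Mann-Whitney test take no covariate, so the second score can be used only after the test itself is changed, and most of that change's benefit may come from adjusting for baseline. Under serial decay the second score adds nothing.

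All of this stands, and it sets the weight of the point. It does not remove it: the article fixes an unadjusted single-baseline comparison although a second pre-treatment measure of the primary outcome is on the schedule.

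A reader might infer more than the documents support:
- That the gain is a fixed 25% (0.75/1.00 or 0.30/0.40 in the table), as if 200 children did the work of 200/0.75 ≈ 267. This needs the earlier rating to predict post-treatment as well as the later one does. Nothing in the article establishes that, and the mean-of-two approach behind the figure can lose precision.
- That every child already has two usable subscale scores in the database. Eligibility needs only the ABC total, and the article does not say that the recruitment subscale is entered or that the same parent completes both ratings.
- That the recruitment score is discarded. The article only gives it no stated analytic role.
- That selection on the total biases the comparison. It does not, because it precedes randomisation.

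**Conclusion.** The point holds as a modest one about efficiency. A scheduled pre-treatment rating of the primary outcome has no stated place in an unadjusted primary comparison, so some rating error that could be removed may stay in. Beyond baseline adjustment, the second covariate cuts residual variance by between nil and about 20% over the correlations tried. These assume equal variances and rest on no figure in the documents; the interval between the two pre-treatment ratings is also not given.

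If the SD of change is 5, the practical effect is about one point of power or less. If it is nearer 8, the recruitment rating adds between 0 and about 8 points to what ANCOVA on baseline would achieve. The validity of the randomised comparison is not in question.

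**What to change.** Make the primary analysis an ANCOVA of the post-treatment hyperactivity-noncompliance score on treatment, with the baseline score and the recruitment score of the same subscale as pre-specified covariates. Apart from the degree of freedom used, the second covariate cannot raise the residual variance, so the choice is safe even if it turns out to add nothing.

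Do not use the mean of the two ratings as the reference for a change score. It alters the stated outcome and can increase the variance.

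The cost is a change of primary test from t-test or Mann-Whitney to ANCOVA, one degree of freedom for the recruitment score, and entry of the recruitment subscale score as well as the total.

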### Objectives of the study

The primary objective of this study is to evaluate the effectiveness of the «COGNITUS & MOI» program compared to a motor skill and video viewing intervention in terms of children’s behavioral problems.

The secondary objectives are as follows:to investigate the effectiveness of the «COGNITUS & MOI» program compared to a motor skill and video viewing intervention on children’s neurocognitive abilities;to investigate the effectiveness of the «COGNITUS & MOI» program compared to a motor skill and video viewing intervention on functional outcomes in children (adaptive behaviors, quality of life and self-esteem); andto evaluate the long-term maintenance (6 months after) of the beneficial effects of these treatments.

It is hypothesized that children who undergo the «COGNITUS & MOI» program will demonstrate greater and more sustainable improvements in behavioral problems, neurocognitive abilities and functional outcomes than those who receive a motor skill and video viewing intervention.

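### The 6-month maintenance objective is tested only on change since post-treatment, so no planned analysis estimates the treatment effect still present at 6 months

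*Protocol article*

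**What the plan says.** All places are in the Protocol article.

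- **Objectives of the study.** The third secondary objective is to "evaluate the long-term maintenance (6 months after) of the beneficial effects of these treatments". The hypothesis is that children given COGNITUS & MOI "will demonstrate greater and more sustainable improvements in behavioral problems, neurocognitive abilities and functional outcomes than those who receive" the control intervention.
- **Assessments and outcomes.** The secondary outcome that covers follow-up is the "change of all scores from post-treatment to the 6-month follow up". It applies to all scores, so it includes the hyperactivity-noncompliance subscale that serves as primary outcome.
- **Statistical analysis.** The primary test compares the "score change from the baseline to post-treatment assessment in the two groups". The section continues: "Third, similar tests will be run for each secondary outcome measure", and then: "The score changes will be separately considered from the baseline to post-treatment assessment and from the post-treatment to 6-month follow-up assessment".
- **Table 2.** Every outcome measure is collected at baseline, post-treatment and 6-month follow-up.

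The outcome list also speaks of change from baseline without naming a visit. The Statistical analysis section settles this, because the only interval that starts at baseline ends at post-treatment. No comparison of the arms from baseline to 6 months, or at 6 months, is stated.

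**The concern.** A family or clinician asking about maintenance wants to know whether children given COGNITUS & MOI are still better off than control children 6 months later. That is a between-arm difference measured from before randomisation. The plan starts the follow-up contrast at the post-treatment score, which treatment has already affected. The result describes how the arms diverge or converge afterwards, and the benefit already gained drops out of it.

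This follows from contrasts that the outcome list and the analysis section both fix; it is not a detail left open for a later document. At stake is the third secondary objective: the trial could end with a significant follow-up result in control's favour, and no planned estimate or interval to show that COGNITUS & MOI was still ahead.

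**Working it through.** **Inputs from the Sample size section.** Expected change is -3 points in control and twice that, -6, for COGNITUS & MOI, so that "the difference between the two treatments would be at least 3 points". SD is 5, power 90%, two-sided 5%, 1:1 allocation; 126 participants are required and 200 are enrolled (100 per arm).

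**Inputs that are assumed.** The protocol gives no expected 6-month values, no SD for change after post-treatment and no dropout rate. The 6-month means below are illustrations. SD 5 is carried over to every change score, and a wider SD is tried at the end.

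**The plan's own figure.** The normal formula gives n = 2 × [5 × (1.960 + 1.282)/3]² = 58.4, so 59 per arm (118 in total). The exact t-test gives 59.35, so 60 per arm (120). Dividing by the Mann-Whitney efficiency, 59.35/(3/π) = 62.15, so 63 per arm, which is 126. The protocol names the Mann-Whitney test but not this correction, so the route is inferred. The present point does not depend on it.

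**Identity.** Let D be the mean change for COGNITUS & MOI minus that for control; negative values favour COGNITUS & MOI. Then

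D(post to 6 months) = D(baseline to 6 months) − D(baseline to post).

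Under full maintenance the two terms on the right are equal (−3 and −3), so the planned contrast has expectation 0. If the program never worked, it is 0 − 0 = 0. In both cases it rejects 5% of the time.

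**Probability of significance in a given direction.** Φ(|D|/SE − 1.960), with SE = SD × √(2/n). With SD 5, SE = 0.707 at 100 per arm and 0.891 at 63 per arm.

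**Main illustration.** COGNITUS & MOI is at −6 at post-treatment and −4 at 6 months; control is at −3 and −3.

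- D(baseline to 6 months) = −4 − (−3) = −1, so COGNITUS & MOI is still ahead.
- D(post to 6 months) = +2 − 0 = +2, in control's favour.
- At 100 per arm: 2/0.707 = 2.828; Φ(0.868) = 0.807 (0.804 by the t-test).
- At 63 per arm: 2/0.891 = 2.245; Φ(0.285) = 0.612.

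**Other assumed courses, 100 per arm, SD 5, starting from −6 v −3 at post-treatment**

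| Course after treatment | D, baseline to 6 months | Chance significant for COGNITUS & MOI | D, post to 6 months | Chance significant for control |
|---|---|---|---|---|
| No later change | −3 | 98.9% | 0 | 2.5% |
| COGNITUS & MOI loses 1, control 0 | −2 | 80.7% | +1 | 29.3% |
| Both arms lose half their gain | −1.5 | 56.4% | +1.5 | 56.4% |
| Both arms lose all their gain | 0 | 2.5% | +3 | 98.9% |

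If both arms fade in proportion, the arm that gained more always shows the larger loss.

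**Sensitivity to the SD.** The only other SDs in the protocol are 8.9 and 7.4, reported with the mean scores of the cited study. Pooled: √[(8.9² + 7.4²)/2] = 8.18. These belong to scores, not changes, so they serve only as a wide value. For the main illustration, SE = 8.18 × √(2/100) = 1.157 and Φ(1.728 − 1.960) = 0.41; at 63 per arm, SE = 1.458 and Φ(1.372 − 1.960) = 0.28. The chance therefore runs from about 28% to 81% over these inputs. The sign of each contrast does not change.

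**The case against.** The follow-up contrast is not meant to stand alone. The baseline to post-treatment test comes first and is there to detect a program that does not work, so the fact that full maintenance and no effect both give 0 matters less once both results are read together. With mean changes and complete data, the two differences add up to the baseline to 6-month difference (−3 + 2 = −1 in the illustration). The contrast also has the right sign for what it measures: in that example COGNITUS & MOI did lose more after treatment, which bears on the part of the hypothesis about sustainability.

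Most of this stands, and it limits the point. A reader might infer that the plan can never show lasting benefit, that the test gives a wrong sign, or that it would declare the program worse than control. The documents support none of these. A reader might also infer that a non-significant result will be taken as proof of maintenance, but the protocol states no such rule.

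What remains is that no test or interval is planned for the sum. Its standard error cannot be obtained from the two separate tests without the covariance of the two changes. The sum does not work for Mann-Whitney results, or where different children complete each visit, and the protocol itself expects dropout. Nor does a significant first test followed by a non-significant second one settle the matter: a true loss of 1.5 of the 3 points would be missed in about 44% of trials (1 − 0.564).

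**Conclusion.** The point holds in this form: the planned 6-month analysis measures relative loss or gain since post-treatment and does not estimate the between-arm difference at 6 months relative to baseline. That part rests on the stated contrasts and the identity alone. The probabilities are illustrative: about 80% for a result in control's favour while COGNITUS & MOI is still 1 point ahead, given assumed 6-month means, SD 5 for the later change and 100 per arm without dropout; about 61% at 63 per arm, and lower with a wider SD.

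The recommended contrast brings no gain in power when little benefit is left: a remaining 1.5 points is detected with about 56% probability and a remaining 1 point with about 29% (SD 5, 100 per arm). Its advantage is that it estimates the quantity the objective names.

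This should be fixed. It touches one secondary objective; the primary outcome, its test and the sample size are unaffected.

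**What to change.** Name, as the maintenance analysis, the between-arm difference in change from baseline to 6 months for each outcome, preferably adjusted for the baseline score, with a 95% confidence interval. Keep the post-treatment to 6-month change as a supportive description of relative loss or gain, and state that its non-significance is not evidence of maintenance. A single repeated-measures model over both visits would be one way to do this, but the defect does not require it.

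The cost is one more secondary comparison per outcome and a few changed sentences in the outcome list and the analysis section. Table 2 already schedules every outcome measure at all three assessments, so no new data are needed.

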## Discussion

Drug treatments are often unsatisfactory methods to overcome challenging behaviors in children with mild to moderate ID. Cognitive remediation could be a promising alternative. To our knowledge, no program has been designed and validated for this clinical population. It is thus of great importance to undertake a treatment-efficacy study. The «COGNITUS & MOI» study specifically investigates the efficiency of a cognitive remediation program designed for children with mild to moderate ID.

The primary strength of this study is the «COGNITUS & MOI» program itself. It is of particular interest in ID considering that these patients have heterogeneous cognitive profiles, have few adaptive skills in daily life, and often feel incompetent. The «COGNITUS & MOI» program allows for the precise adaptation to individual clinical and cognitive profiles. Furthermore, it is based on active coaching that favors positive reinforcement and metacognitive training. It aims at improving daily life by encouraging strategy transfer. The partnership with the parents must also be emphasized because it allows for the consideration of the context of the child’s family unit. The randomized design is another strong point of the present study, highlighting the specific effect of the «COGNITUS & MOI» program versus a nonspecific intervention. It is well-known that ‘therapeutic alliance’ explains a significant proportion of any behavioral therapy efficiency. Therefore, it is very important to differentiate these general effects to validate the «COGNITUS & MOI» cognitive remediation program. The evaluation of the long-term maintenance of beneficial effects is also of particular relevance.

One limitation of this study may be that the primary outcome is assessed in an open-label fashion. Parents score their children using the ABC scale and know the intervention their child received. The use of this kind of measure is nevertheless fully justified by the fact that the study takes into account functional outcomes in everyday life, and parents receive standardized instructions to limit potential biases. Another limitation could concern the feasibility of the cognitive remediation program in children with ID. For example, it would be fair to question the use of metacognitive questioning with these children and their attendance throughout the program. Preliminary case studies confirm that the «COGNITUS & MOI» program is fully adapted to this clinical population, even in the case of poor verbal expression abilities.

